#### Secondary outcomes

##### Maternal outcomes

The implantation rate is defined as the number of gestational sacs in the uterus divided by the number of embryos transferred. The live birth rate is defined as the delivery of any viable infant at 25 weeks of gestation or more after initial embryo transfer to the number of transplant cycles. The biochemical pregnancy rate is defined as the ratio of biochemical pregnancies (serum hCG level >5 mIU/L 14 days after embryo transfer) to the number of transplant cycles. The spontaneous abortion rate is defined as the ratio of spontaneous abortions (spontaneous pregnancy loss before 20 weeks of gestation) to the number of transplant cycles. The ongoing pregnancy rate is defined as the ratio of ongoing pregnancies (intrauterine live fetus under ultrasonography after 20 weeks of gestation) to the number of transplant cycles. The preterm birth rate is defined as the ratio of preterm births (delivery at ≥ 28 and < 37 weeks of gestation) to the number of transplant cycles. Pregnancy complications, including GDM, hypertensive disorders of pregnancy, including gestational hypertension and preeclampsia, placental abruption, preterm/prelabor/rupture of membranes, birth mode (vaginal delivery/operational vaginal delivery/selective or emergency cesarean section), blood loss during birth, and postpartum hemorrhage, adherence to the intervention and maternal mortality, will be followed up and assessed. A GDM diagnosis will be made according to the diagnostic criteria of the American Diabetes Association based on the results of the 75-g oral glucose tolerance test (OGTT) at 24–28 gestational weeks (fasting venous glucose level ≥ 5.1 mmol/L, 1-h value ≥ 10.0 mmol/L, 2-h value ≥ 8.5 mmol/L) [21]. Gestational hypertension is defined as de novo hypertension (≥ 140/90 mmHg) after 20 gestational weeks without proteinuria. Preeclampsia will be diagnosed when gestational hypertension is comorbid with any of the following manifestations: proteinuria (≥ 0.3 g/24 h), renal insufficiency, thrombocytopenia (platelets ≤ 100,000 × 10^9^/L), impaired liver function or pulmonary edema [22].

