### Data collection

At the time of enrollment, information about the history of PCOS diagnosis, menstrual cycle demographic characteristics, socioeconomic status, alcohol consumption, smoking habit, self-reported morbidity, obstetric history, first-degree family history of hypertension, diabetes, stroke, hyperlipidemia, and obesity will be obtained using a baseline questionnaire. Clinical information on the maternal and neonatal outcomes mentioned above will be collected from outpatient and inpatient electronic records in four centers and will be confirmed by the investigators.

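### In the preeclampsia definition the platelet number and unit do not match, so the printed thrombocytopenia limit is 1,000 times too high and excludes no one (minor)

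*Protocol article*

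**What the plan says.** All of the definition stands in the protocol article under Secondary outcomes, Maternal outcomes. The pregnancy complications to be followed up include "hypertensive disorders of pregnancy, including gestational hypertension and preeclampsia".

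- **Gestational hypertension:** "Gestational hypertension is defined as de novo hypertension (≥ 140/90 mmHg) after 20 gestational weeks without proteinuria".
- **Preeclampsia:** "Preeclampsia will be diagnosed when gestational hypertension is comorbid with any of the following manifestations". Five signs follow: proteinuria, renal insufficiency, a low platelet count, impaired liver function and pulmonary edema.
- **The platelet sign:** "thrombocytopenia (platelets ≤ 100,000 × 10^9^/L"). This is the only place where a platelet limit appears, and nothing elsewhere in the article corrects it.

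On the source of these outcomes, the Data collection section says that clinical information on maternal and neonatal outcomes "will be collected from outpatient and inpatient electronic records in four centers and will be confirmed by the investigators".

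**The concern.** The printed limit pairs a number that belongs to a per-microlitre count with a per-litre unit. The result is a limit for a low platelet count that no count can exceed, so the figure contradicts its own label.

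The slip matters more here than it would in background text because it sits in an outcome definition, and in one where a single sign is enough. A sign that is always present satisfies such a rule by itself. What is at stake is the separation of two named secondary outcomes. A person or program that applies the printed figure would classify women differently from one that silently corrects the unit, and the article gives the four centres no correct written figure to work from.

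**Working it through.** **Inputs**

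- Printed limit: 100,000 × 10^9/L (Maternal outcomes).
- Combination rule: gestational hypertension plus at least one of five signs (Maternal outcomes).
- Conversion: 1 L = 10^6 µL.
- Assumptions, not in the documents: a deliberately wide range of platelet counts, 20 to 2,000 × 10^9/L, and a platelet volume of 7 to 12 fL (1 fL = 10^-15 L).

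**Step 1. The limit as printed**

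100,000 × 10^9/L = 10^5 × 10^9/L = 10^14 per litre.
Per microlitre: 10^14 / 10^6 = 10^8, that is 100,000,000 per µL.

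**Step 2. The same number with a per-microlitre unit**

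100,000 per µL × 10^6 µL/L = 10^11 per litre = 100 × 10^9/L.

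**Step 3. Ratio**

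10^14 / 10^11 = 1,000, exactly.

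**Step 4. Does the printed limit exclude anyone?**

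| Count (× 10^9/L) | Meets the printed limit | Meets 100 × 10^9/L |
|---|---|---|
| 20 | yes | yes |
| 50 | yes | yes |
| 99 | yes | yes |
| 100 | yes | yes |
| 150 | yes | no |
| 250 | yes | no |
| 450 | yes | no |
| 1,000 | yes | no |
| 2,000 | yes | no |

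As a check on physical possibility, platelets at the printed limit would occupy 10^14 × 7 × 10^-15 L = 0.7 L per litre of blood at 7 fL each, and 10^14 × 12 × 10^-15 L = 1.2 L per litre at 12 fL. No real count comes near this, so the printed sign is true for every woman.

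**Step 5. Consequence under the combination rule**

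Let G be the women with gestational hypertension and S1 to S5 the five signs. The rule is: preeclampsia = G and (S1 or S2 or S3 or S4 or S5). With the platelet sign always true, the bracket is always true, and preeclampsia = G. Read literally, the two groups are the same women. With the limit at 100 × 10^9/L the bracket again depends on findings in the individual woman.

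**Step 6. How many women could be involved**

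This is an illustration. The Sample size calculation section gives clinical pregnancy rates of 17.65% and 41.82% in two PCOS groups. Applied to 300 women: 300 × 0.1765 = 53 and 300 × 0.4182 = 125 clinical pregnancies. If 5% to 15% of these had a hypertensive disorder (an assumption; the article gives no rate), that is 53 × 0.05 ≈ 3 to 125 × 0.15 ≈ 19 women in both arms together.

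**The case against.** The strongest reply is that the slip corrects itself. The sign is named thrombocytopenia and the figure only glosses it in parentheses. A clinician would not call a normal count thrombocytopenia, and would not diagnose preeclampsia in every hypertensive woman on the strength of this sentence. The Data collection section points the same way, since outcomes are taken from clinical records and confirmed by investigators. This stands, and it is why the point is minor.

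Three further readings are tempting, and the document does not support them.

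- **That all gestational hypertension will in fact be counted as preeclampsia.** This needs a step that derives the diagnosis from laboratory values by the printed rule. None is described. The electronic platform (CRIP) appears in the article for data entry, storage and allocation, and no automatic derivation or edit check for preeclampsia is mentioned.
- **That the gestational hypertension outcome would be left empty.** The text builds preeclampsia on gestational hypertension and does not say that women with preeclampsia are removed from the gestational hypertension count. Read literally, the two counts would be equal. Emptiness would need an added rule that the categories exclude each other.
- **That safety reporting is compromised.** Under Data monitoring and auditing, harms are classified by CTCAE Version 5, and this definition is not used there.

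It can also be said that a strictly literal reading of the sentence already fails for another reason: gestational hypertension is defined by absence of proteinuria, and proteinuria is then listed as a sign that turns it into preeclampsia. That makes mechanical coding of the sentence less plausible. It does not make the platelet figure right.

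What the reply leaves standing is the error itself. The number and unit are wrong as printed, they sit in the rule by which preeclampsia is to be diagnosed, and nothing else in the article corrects them. Nor is it a matter that a fuller document would simply supply, because the article states the figure and states it wrongly.

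**Conclusion.** The point holds as a unit error of minor severity. The printed limit is 1,000 times the value that 100,000 per microlitre would give, and it excludes no one. That part is exact and needs no assumption beyond the obvious one that real platelet counts lie far below 10^14 per litre.

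The loss of distinction between gestational hypertension and preeclampsia is conditional: it follows if the printed rule is applied literally, and it is not a forecast of what the centres will do. At most a small number of women would be affected, about 3 to 19 in the trial under the assumed rates above. The primary outcome, the sample size, eligibility and randomization are untouched.

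That the intended limit is 100 × 10^9/L is an inference from the number 100,000 and the label. The criteria that the article cites for this definition are not at hand, so the value has to be confirmed against them.

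**What to change.** Reconcile the number and the unit in the preeclampsia definition with the criteria cited there, and print the limit in one consistent unit (apparently 100 × 10^9/L, which is the same as 100,000 per microlitre). Give the corrected limit to all four centres as the standard for investigator confirmation. If preeclampsia is derived by program anywhere, in CRIP or in the analysis, check that the derivation uses the same limit. Where diagnoses have already been confirmed, ask whether any rested on the platelet sign alone, and recheck only those.

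The cost is one edited figure, a short note to the centres and a check of any derivation. Nothing in the design, the treatment or the sample size changes.

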##### Neonatal outcomes

The birth defect rate is defined as the ratio of birth defects (fetal body structure, functional or metabolic congenital abnormalities) to the number of transplant cycles*.* Birth weight, infant sex, gestational age at birth, Apgar score, congenital anomalies, shoulder dystocia, bone fracture, neonatal hypoglycemia, bronchial plexus injury, neonatal respiratory distress, neonatal pathological jaundice, neonatal intensive care unit admission, stillbirth (≥ 20 weeks), and neonatal death (within the first 28 days after delivery) will be followed-up and assessed.

### Microbiome and metabolism

Alpha and beta diversity analysis will be conducted by QIIME2 software [23]. The taxonomy abundance spectrum will be described and compared between groups using the linear discriminant analysis effect size (LEfSe) method. Metabolic profiles will be analyzed using the Progenesis QI v3.0 software.

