**Methods/design:**

This is a protocol for a multicenter, open-label, randomized controlled trial in China. Women diagnosed with PCOS who are undergoing IVF-FET treatment will be recruited. Allocation to the intervention/control arms at a ratio of 1:1 will be executed by an electronic randomization system. Participants in the intervention arm will receive the live *Lactobacillus* capsule vaginally for 10 consecutive days before embryo transfer, while those in the control arm will receive standard individualized care. The primary outcomes will be the clinical pregnancy rate, implantation rate, and live birth rate. 16S rRNA sequencing and liquid chromatography–mass spectrometry will be conducted to evaluate the LGT microbiome and systemic metabonomics before and after the intervention. A sample of 260 participants will provide 95% power to detect a 20% increase in the rate of clinical pregnancy (*α* = 0.025, one-tailed test, 15% dropout rate). A total of 300 participants will be recruited.

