## Methods/design

### Objectives

We plan to conduct the present trial to evaluate the effects of supplementation with live *Lactobacillus* capsules for vaginal use on reversing LGT dysbiosis and improving perinatal outcomes in PCOS patients undergoing IVF-FET.

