### Participants

#### Inclusion criteria

A total of 20- to 35-year-old women who have been diagnosed with PCOS according to the Rotterdam Criteria and plan to undergo IVF–FET will be recruited. Quick screening of the abundance of *Lactobacillus* spp. will be performed by real-time quantitative polymerase chain reaction (RT–qPCR), which will be specified later. Women with PCOS with *Lactobacillus* spp. accounting for less than 80% of the vaginal microbiome who volunteer to participate will be eligible for this study.

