### Sample collection

Two vaginal swabs, 2 cervical canal swabs, and 3 ml of peripheral blood will be collected on the day of the first clinic visit and the day of embryo transfer (ET). Vaginal swabs will be collected directly, while cervical canal swabs will be collected carefully through a vaginal dilator device to avoid contamination from contact with the vagina. Vaginal and cervical canal swabs will be immediately collected in a clean 2-ml DNA LoBind tube and immediately placed on ice and transferred to a − 80 °C freezer within 2 h, followed by DNA extraction. Peripheral venous blood will be collected in coagulation-enhancing disposable vacuum blood collection tubes. Blood will be centrifuged at 2000 rpm for 20 min at 4 °C (Eppendorf, Germany). Serum will be isolated and divided into 2 tubes and immediately frozen at − 80 °C until use.

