### Participant timeline

The time schedule of enrollment, intervention, follow-up and outcome assessments is shown in Table 3. After undergoing ovulation, egg retrieval, IVF, and advanced embryo freezing, PCOS patients will move on to the next step of endometrial preparation for FET. The duration of endometrial preparation will continue for approximately 14 days. At the 1st clinical visit on the first day of the current FET cycle, written informed consent, baseline information, 2 vaginal swabs, 2 cervical canal swabs, and 3 ml peripheral blood will be obtained at enrollment. After quick screening for the relative abundance of *Lactobacillus* spp. in vaginal flora, the participants will be informed of whether they have LGT dysbiosis and the results of randomization. At the 2nd visit after enrollment, in the control group, participants with LGT dysbiosis will confirm the next contact, while the intervention group will administer live *Lactobacillus* capsules vaginally and will be provided a medication diary. All participants will be followed up 5 times in the clinic or by phone call. The 3rd visit after 5 days of drug administration will mainly be about whether any adverse response occurs. At the 4th visit after 10 days of drug administration, the medication diary will be checked and reviewed, and any adverse response will be recorded and reported. At the 5th visit on the day of ET, 2 vaginal swabs, 2 cervical canal swabs, and 3 ml peripheral blood will be obtained from participants in both groups. At the 1st follow-up after 14 days of ET, human chorionic gonadotropin (HCG) and progesterone (P) levels will be determined as standard clinical procedures. If the HCG test is positive, the 2nd follow-up will occur approximately 5 weeks after ET, and clinical pregnancy will be confirmed by ultrasound and recorded in the CRIP system. At the 3rd follow-up, the fetal developmental situation and maternal obstetric complications at approximately 24-28 gestational weeks, if any, will be carefully recorded. The endpoint of follow-up is live birth, and maternal and neonatal information will be obtained.

**Table 3 Tab3:** Schedule

	1st visit on FET initial day	2nd visit after enrollment	3rd visit after 5 days	4th visit after 10 days	5th visit on ET	1st follow-up at 14 days after ET	2nd follow-up at 5 weeks after ET	3rd follow-up at mid-pregnancy	End of live birth

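### Reversing dysbiosis is the first-named objective, but no listed outcome measures it, and the one taxonomic method named (LEfSe) gives no between-arm Lactobacillus effect with a confidence interval

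*Protocol article*

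**What the plan says.** All references are to the Protocol article.

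- **Objectives.** The trial is to evaluate the capsule's effects "on reversing LGT dysbiosis and improving perinatal outcomes in PCOS patients undergoing IVF-FET". Reversal comes first.
- **Abstract, Methods/design.** Sequencing and mass spectrometry "will be conducted to evaluate the LGT microbiome and systemic metabonomics before and after the intervention".
- **Sample collection, Participant timeline and Table 3.** Swabs are taken at the first visit and again on ET day. At the second of these, "2 vaginal swabs, 2 cervical canal swabs, and 3 ml peripheral blood will be obtained from participants in both groups". Table 3 puts allocation at the second visit, so the first swab precedes it.
- **Inclusion criteria.** Eligible women have Lactobacillus "spp. accounting for less than 80% of the vaginal microbiome", measured by the qPCR screen.
- **Primary outcome, Maternal outcomes, Neonatal outcomes.** The primary outcome is clinical pregnancy. The secondary lists are long and detailed. They contain no Lactobacillus, diversity or dysbiosis measure.
- **Microbiome and metabolism.** "Alpha and beta diversity analysis will be conducted by QIIME2 software", and then: "The taxonomy abundance spectrum will be described and compared between groups using the linear discriminant analysis effect size (LEfSe) method". The section does not say which swab is compared or what the baseline swab is used for.
- **Statistical analysis.** Outcomes collected at several time points are to be fitted by GEE. Binary endpoints get risk ratios with 95% confidence intervals, with and without adjustment for baseline values. Neither rule mentions the microbiome.

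**The concern.** The plan names an aim, collects the data for it in both arms, and then attaches a method that answers a different question. LEfSe screens many taxa for those that discriminate between groups. A report that followed the section on Microbiome and metabolism could list the taxa that differ. It would not have to say by how much the Lactobacillus share differed between arms, or with what uncertainty.

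Two things depend on that estimate.

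- **The reversal claim itself.** No measure of reversal is fixed. The article contains two cut-offs for Lactobacillus (below 80% for eligibility, below 50% for deficiency in the sample size text) and two swab sites (vaginal, cervical). On the sequencing data alone that is 2 × 2 = 4 possible definitions, none chosen, in a trial whose investigators know the allocation.
- **The reading of the pregnancy result.** The rationale is that restoring Lactobacillus raises the pregnancy rate, and the Discussion concedes that controls can still obtain Lactobacillus. If pregnancy does not differ, the first question will be whether the flora differed between arms. That calls for a between-arm estimate with an interval, which a list of taxa does not supply.

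**Working it through.** **The plan's own figure.** The article gives no power or effect size for any microbiome measure. Its only sample size, 260 (130 per group) with 300 to be recruited, is for clinical pregnancy. Taking the article's rate of 17.65% for Lactobacillus-deficient patients, and reading the 20% increase as 20 points (37.65%), with one-sided alpha 0.025, 95% power and pooled variance under the null:

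n per arm = [1.960 × √(2 × 0.2765 × 0.7235) + 1.645 × √(0.1765 × 0.8235 + 0.3765 × 0.6235)]² / 0.20² = 127

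That is 254 in total, close to 260. With 15% dropout, 127 / 0.85 = 149.4, so 150 per arm and 300 in total. The figure reproduces on these inputs (the article does not say which control rate it used) and has no bearing on the microbiome.

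**Objective against outcome and method.**

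| Needed to report reversal | What the article fixes |
|---|---|
| A listed outcome | None in the primary, maternal or neonatal lists |
| Swab site and time point for the comparison | Not stated |
| Role of the baseline swab | Not stated |
| Between-arm effect with 95% CI | Not given by LEfSe; possible under the GEE or risk-ratio rules only once an endpoint is defined |

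**What an unadjusted ET-day comparison would cost.** Let rho be the correlation between the baseline and ET-day Lactobacillus share, on a suitable scale. Adjusting for baseline multiplies the variance of the between-arm difference by 1 − rho². Equivalently, the unadjusted analysis has 1/(1 − rho²) times the adjusted variance. The article gives no rho, so a range is assumed. For scale, 300 × 0.85 = 255 evaluable women, or about 127 per arm, give an unadjusted 95% half-width of 1.96 × √(2/127) = 0.246 SD. The adjusted half-width is 0.246 × √(1 − rho²).

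| Assumed rho | 1 − rho² | 1/(1 − rho²) | Adjusted half-width (SD) |
|---|---|---|---|
| 0.3 | 0.91 | 1.10 | 0.235 |
| 0.5 | 0.75 | 1.33 | 0.213 |
| 0.7 | 0.51 | 1.96 | 0.176 |

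**Validity and power.** A simulation compared a Kruskal–Wallis test on the ET-day value alone (taken as the univariate step of LEfSe) with a baseline-adjusted ANCOVA. It assumed a normal outcome, 127 per arm and two-sided alpha 0.05, with 4,000 runs per setting.

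- With no true difference, both tests rejected in about 5% of runs (0.046 to 0.049 for Kruskal–Wallis).
- With a true difference of 0.35 SD, the ET-day-only test had power of about 0.77. ANCOVA had 0.83, 0.89 and 0.97 at rho 0.3, 0.5 and 0.7.

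Omitting baseline therefore costs precision and does not bias the randomised comparison.

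**The case against.** The case against making much of this is strong on several points.

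- **The GEE rule may cover it.** Swab measures are taken at two visits, so the rule for outcomes at different time points could apply by its wording. This stands as a possibility, and it rules out saying that LEfSe is the only analysis intended. It does not close the gap: the rule does not name the microbiome, and the variable, site and contrast would still be undefined.
- **The section is silent on baseline.** A reader might infer that the baseline swab is ignored. The text does not say so, and the abstract promises an evaluation before and after treatment. The supportable statement is that the swab has no stated role.
- **LEfSe does yield an effect size.** It gives an LDA score per taxon. What it lacks is an interpretable treatment effect on Lactobacillus with a confidence interval.
- **Regression to the mean.** Women are selected for a low screening value, so a reader might expect a spurious recovery. The stated comparison is between randomised groups, where such recovery is expected equally in both arms and cancels. It would matter only if the claim were rested on within-arm change, which the article does not plan.
- **Model detail belongs in an analysis plan.** The choice of ANCOVA, the transformation and the covariates can fairly be left to a document not shown. The outcome list is different: the article sets it out at length, and it fixes LEfSe by name.
- **The correlations are generic.** They are assumed. Because eligibility caps the baseline below 80%, the true correlation may be lower, and 0.7 may be optimistic.

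**Conclusion.** The point holds as a mismatch between the first-named objective and what is measured and estimated for it. No listed outcome captures reversal, and the taxonomic method named does not produce the between-arm estimate that a reversal claim needs.

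A reader might go further and infer that the trial cannot answer its first objective. The documents do not support that. Both arms are randomised and swabbed before allocation and on ET day, so the data suffice. Even an unadjusted ET-day comparison would be valid.

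The measurable cost of leaving out the baseline is a variance 1.10 to 1.96 times that of the adjusted analysis, for assumed correlations of 0.3 to 0.7. The power figures rest further on normality and an assumed difference of 0.35 SD, so they are illustrations and not forecasts. The primary analysis of clinical pregnancy is not affected. This is a cheap improvement.

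**What to change.** 1. Add one secondary endpoint: Lactobacillus share of the vaginal microbiome on the ET-day swab, from the 16S sequencing already planned.
2. Compare it between arms as randomised, with the baseline share as covariate, and report the difference with a 95% CI. ANCOVA on a suitable transformation will do, as will the article's GEE with a baseline term. Say that the article's multiple imputation rule applies to women without an ET-day swab.
3. Base any statement about reversal on this between-arm estimate and not on within-arm change from before to after.
4. Keep LEfSe and the diversity analyses, labelled exploratory.
5. If a responder figure is wanted, report the risk ratio for reaching at least 80% as supportive only. That cut-off comes from the qPCR screen and may not carry over to 16S data, so the continuous analysis should lead.

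The cost is one more secondary endpoint and one extra model, with no new samples or assays. The wording should be settled before any comparison of the arms is run.
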